### Eligibility criteria

All participants and their legal guardians have to provide a sufficient understanding of the German language and a declaration of informed consent before taking part in the study. The study protocol has been approved by the ethical committee of the University of Regensburg. The experimental group will consist of children and adolescents meeting the criteria of an anxiety disorder according to the classification systems DSM-IV and ICD-10. Included diagnoses are Agoraphobia (ICD-10 F40.0) with/without panic disorder (F40.00, F40.01), social phobia (F40.1), panic disorder (F41.0), generalized anxiety disorder (F41.1), separation anxiety disorder of childhood (F93.0) as well as social (F93.2) and generalized (F93.80) anxiety disorder of childhood. The categorical diagnoses of diseases will be assessed using the semi-structured diagnostic interview M.I.N.I-KID 6.0 [44]. Anxiety-questionnaires (BAI [45], BDI-II [46], STAI [47], SPAIK [48], SCARED-D [49, 50]) will be administered to measure the symptomatology of anxiety dimensionally. Exclusion criteria will be IQ < 85 [assessed by the Wechsler Intelligence Scale-V (WISC-V), 4 subtests: Similarities, Vocabulary, Matrix Reasoning, Block Design; 11–16 years [51]; > 16 years [52]], pubertas praecox vera [53], pregnancy, current glucocorticoid-containing medication, known genetic syndromes, history of traumatic brain injury, history of endocrinological disorder, any other chronic neurological disorder which influences the brain development and physiology, acute suicidal behavior and any current and history of psychiatric disorder according to DSM-IV and ICD-10 except mild depressive episode (ICD-10 F32.0) and moderate depressive episode (F32.1). Patients with mild and moderate depressive episodes were included because of the high comorbidity rate between anxiety disorders and depression [5]. Hormonal contraceptives and psychotropic medication will be noted and corrected for but are no exclusion criteria. The healthy control group will be matched according to sex, age, pubertal status and school education. For the control group, exclusion criteria additionally include current and history of in- and outpatient psychiatric and psychotherapeutic treatments and any current or lifetime psychiatric disorders.

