### Physiological measures and stress challenge

To minimize the effects of hormone fluctuations caused by the circadian rhythm [32], all participants will start the 2.5 h experimental test session (T2, see Fig. 1) at the same time in the afternoon (4:00 pm). Females who have begun menstruation will be tested in the luteal phase (time after ovulation) of their menstrual cycle, since the CORT stress response of females is more similar to the male reaction in the luteal phase than in the follicular phase [32, 59]. The onset of the female participants' ovulation and the pubertal development will be assessed using the German adaptation [60] of the self-report Pubertal Development Scale [61]. However, in previous studies, no main effect of sex for OXT levels in adolescents was found [32, 62]. Still, to minimize the effect of age and pubertal development [62, 63] both groups will be matched according to pubertal status [61].

At the end of T1, participants and their parents/legal guardians will be instructed to take one saliva sample by themselves at home within a relaxing atmosphere (T2a) and at least one hour after their last food intake. They will be asked to take the sample two days in advance of T2 in the afternoon, at the same time as the experimental test session (T2) takes place (4:00 pm). This will constitute the baseline salivary OXT and CORT level before the experimental test procedure (T2) will be conducted. The experiment will start with a 60 min relaxation period (T2a) to minimize external effects caused by previous food/drink intake, smoking cigarettes or stressful situations. During the experiment, participants will only be allowed to drink water [32]. Participants will be situated in a separate room (Room A) with relaxing material (reading, painting, puzzle, music). After 1 h (− 1 min before TSST start), the first salivary OXT and CORT level will be measured.

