### Statistical analysis

To ensure objectivity the data will be assessed in accordance with the current standards of empirical research. The collected data will be evaluated using SPSS 25.0 (IBM Corp. Released 2017. IBM SPSS Statistics for Windows, Version 25.0. Armonk, NY: IBM Corp.). Using $$x^{2}$$—test for discrete analysis of variance (ANOVA) for continuous variables with group and gender as inter-subject factors, the demographic and psychometric data will be evaluated. The measured OXT and CORT levels will be transformed to achieve normal distribution. Correlations between psychological VAS ratings and OXT and CORT will be explored through Pearson correlations in case of normally distributed data and through Kendall’s τ otherwise. As correlation between OXT and CORT is expected, a rmMANOVA (repeated measures Multivariate Analysis of Variance) will be conducted to test the effects of time as a within-subject factor and group as a between-subject factor on OXT and CORT reactivity. In case of correlation between OXT, CORT and VAS ratings, VAS ratings will be included into the rmMANOVA, otherwise separate ANOVAs with the between-subject factor group and within-subject factor time will be conducted. In case of significant main effects or interactions, False Discovery Rate (FDR) [66] corrected post-hoc tests will be performed. Exploratory post-hoc analyses with FDR corrected p-values testing for effects of sex and age on OXT and CORT reactivity will also be conducted.

OXT and CORT increase will be calculated through area under the curve (AUC) analyses as described in Pruessner et al. [67]. Additionally, delta scores will be computed between the OXT and CORT baseline measure and the highest value for a measure of increase [68, 69] and between the highest OXT and CORT value and the lowest value after stress for a measure of recovery [70]. To determine group differences between OXT and CORT baseline, increase and recovery, MANOVAs will be computed with group as a between-subject factor and sex as a within-subject factor. In exploratory analyses, anxiety and depressive symptomatology scores will be included as covariates. As previous research has identified an effect of contraceptives on OXT baseline levels [38] a separate analysis will be run on female participants.

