It is expected that participants suffering from anxiety disorders show a lower basal OXT level than healthy controls. If this is indeed the case, future studies may be able to achieve a therapeutic effect by raising basal OXT levels in clinical cohorts. As moderate anxiety and a lower basal OXT level correlated with higher OXT release during the TSST in healthy children and adolescents [32], the expected reduced OXT release of participants with anxiety disorders and a high level of anxiety may suggest the presence of a pathological lacking compensation mechanism. Since it has been shown that the OXT level peaks and decreases earlier than the CORT level [32], a present correlation between OXT level and CORT level suggest that OXT may influences the CORT release and subsequently the subjective stress response. Therefore, if less OXT is released, we expect a higher increase of CORT and respectively a higher subjective stress response. Alternatively, attenuated CORT release might support recent findings with the hypothesis of a CORT hypo-responsiveness in patients with anxiety disorder [39, 40, 42]. Identifying whether there is indeed such a relationship between OXT and CORT is crucial for the in-depth understanding of the stress response in children and adolescents suffering from anxiety disorders.

Potential limitations and challenges of the present study include the fact that the hormonal system is influenced by many external factors, such as pubertal status, sex and parent–child attachment. Therefore, a detailed inspection of the eligibility criteria (see Data Assessment) and a corresponding matching of the control group is highly important. All participants will be carefully examined with detailed questionnaires and categorical diagnoses will be assessed using a semistructured diagnostic interview in addition to routine clinical diagnostics.

For the healthy controls, the study provides the benefit of being screened by psychiatric professionals. If an unpredictable psychiatric abnormality is detected, the affected participant can be admitted directly to the in- or outpatient clinic of child and adolescent psychiatry, psychosomatics and psychotherapy at the University of Regensburg and hence receive help.

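### Age and pubertal status, which the protocol matches on because they affect the hormones, enter no main model, so between-subject comparisons lose precision that two covariates could recover

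*Protocol article*

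**What the plan says.** All references are to the protocol article.

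- **Influence on the hormones.** Physiological measures and stress challenge states: "Still, to minimize the effect of age and pubertal development [62, 63] both groups will be matched according to pubertal status". The limitations paragraph of the Discussion says the "hormonal system is influenced by many external factors, such as pubertal status, sex" and parent–child attachment.
- **Control by design.** Eligibility criteria: "The healthy control group will be matched according to sex, age, pubertal status and school education". No matching tolerance or pairing rule is given.
- **Availability.** Age is an eligibility item (11–18 years). For puberty, "pubertal development will be assessed using the German adaptation" of the PDS. Table 1 places the PDS at T1, and the Design section says the procedure applies to both groups.
- **Models.** Statistical analysis plans an rmMANOVA "to test the effects of time as a within-subject factor and group as a between-subject factor on OXT and CORT reactivity", with VAS ratings added if they correlate with the hormones. The MANOVAs of OXT and CORT baseline, increase and recovery use group and sex. Anxiety and depression scores are covariates in exploratory analyses only. The two regressions for CORT increase and CORT recovery contain neither age nor puberty.
- **Only use of age.** "Exploratory post-hoc analyses with FDR corrected p-values testing for effects of sex and age on OXT and CORT reactivity". This covers reactivity, so it does not reach basal OXT, the first question under Objectives.

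**The concern.** Matching brings the group distributions of age and puberty together. It does not take the variance these variables explain out of the residual. That needs the variables in the model, or a term for the matched pair, and the stated models have neither. Over ages 11 to 18, which span puberty, that variance could be appreciable if the protocol's own rationale is right.

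At stake is the precision of the comparisons that rest on between-subject error:
- basal OXT;
- the AUC, delta and recovery measures;
- the overall group effect in the repeated-measures model;
- any dependence of reactivity itself on age or puberty.

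The first three include the analysis of basal OXT and OXT increase that the Power calculation section used to choose N = 64. A second, conditional risk is that any age or puberty difference left after matching passes into the group contrast, with no main model to correct it.

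**Working it through.** **Inputs from the article (Power calculation):** two groups, significance level 0.05, f = 0.25 and total N = 64 for the MANOVA of group and sex on basal OXT and OXT increase. Power of 80% is stated for the other two calculations and assumed here for this one.

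**Inputs not in the article:** R², the share of outcome variance explained by age and PDS beyond sex, assumed 0.10, 0.20 and 0.30. The residual mismatch after matching is assumed where used below.

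**Step 1. The plan's own figure.** Power comes from the noncentral F distribution with λ = N f². At f = 0.25 and 80% power, the smallest total N is 128 for a one-outcome group test and 158 for a two-outcome MANOVA group test, not 64. N = 64 does come out for the two-outcome MANOVA if f² = 0.16 (f = 0.4), with power 0.805. That discrepancy is a separate matter. It explains why the starting power below is low.

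**Step 2. Power at N = 64 without covariates.** λ = 64 × 0.25² = 4.0.
- Two-outcome MANOVA, four group-by-sex cells (sex taken as between-subject): df1 = 2, df2 = 64 − 4 − 1 = 59, power 0.397.
- One outcome, group only: df1 = 1, df2 = 62, power 0.504.

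**Step 3. Power with age and PDS.** λ becomes 4.0/(1 − R²) and two error degrees of freedom are lost (MANOVA df2 = 57, one-outcome df2 = 60). The error SD is multiplied by √(1 − R²). The equivalent unadjusted sample is 64/(1 − R²). For the MANOVA this assumes that R² applies equally to both outcomes.

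| R² (assumed) | λ | Error SD ratio | Equivalent N | MANOVA power | One-outcome power |
|---|---|---|---|---|---|
| 0.10 | 4.44 | 0.949 | 71 | 0.435 | 0.546 |
| 0.20 | 5.00 | 0.894 | 80 | 0.482 | 0.595 |
| 0.30 | 5.71 | 0.837 | 91 | 0.539 | 0.653 |

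If the covariates explain nothing, both power figures fall by less than 0.1 percentage point (0.397 at R² = 0 for the MANOVA, 0.503 for one outcome).

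**Step 4. Where the gain does not apply.** In the time and group-by-time tests each participant is their own reference. A stable difference in hormone level due to age or puberty cancels. Only an effect of age or puberty on the shape of the response would remain in that error.

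**Step 5. Bias if matching is imperfect.** Bias in SD units = standardised mismatch × correlation r with the outcome. R² of 0.10 to 0.30 corresponds to r of about 0.32 to 0.55. An assumed mismatch of 0.2 SD gives 0.2 × 0.32 = 0.064 to 0.2 × 0.55 = 0.11 SD, or 13% to 22% of d = 2f = 0.5. With 32 per group (normal approximation), the type I error would be 5.8% to 7.2%. With no mismatch the bias is zero.

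**The case against.** The strongest reply is that the protocol already controls both variables by matching and names matching as its answer to the confounders. The comparison of demographic and psychometric data by group would show an age imbalance, and age effects on reactivity are then explored. The article may also not list every covariate: it says contraceptives and psychotropic medication will be corrected for, yet names no medication covariate in a model.

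Part of this stands. A reader might infer that the group contrast is biased. The documents do not support that, because they give neither a matching tolerance nor an achieved balance, and good matching leaves only a loss of precision. A reader might also infer that the whole stress-response analysis has an inflated error term. That fails for the time and group-by-time tests, as Step 4 shows. Nor do two statements of the protocol contradict each other here. If an analysis by matched pair were adopted, most of the gain would already be had.

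The rest does not answer the point. Statistical analysis spells out the factors of each main model and names the exploratory covariates, so the omission of age and PDS is a stated choice. Comparing the groups descriptively leaves the residual variance where it is, and the age exploration omits basal OXT.

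**Conclusion.** The point holds as a precision improvement of unknown size. For the two-outcome MANOVA at f = 0.25 and N = 64, adjustment would raise power from about 40% to about 44%, 48% or 54% at assumed R² of 10%, 20% or 30%. The one-outcome figures, about 50% rising to between 55% and 65%, describe a simpler test than the one planned. These results rest on R² values that the documents do not supply. Adjustment does not bring power to 80% at f = 0.25 in any of these cases, so it is no remedy for the sample size. Protection against residual mismatch is a further benefit, but only if mismatch occurs. A reader might conclude that the plan is invalid without these covariates; it is not.

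**What to change.** In Statistical analysis, prespecify mean-centred age and PDS score as covariates in the MANOVAs of OXT and CORT baseline, increase and recovery, and in the rmMANOVA (or the rmANOVA that replaces it). Centring keeps the meaning of the time test, since covariates in a repeated-measures model bring covariate-by-time terms.

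Keep both covariates however strongly they correlate. Collinearity between them does not harm the group estimate, and a rule that drops one would leave the main model to be chosen after seeing the data. Report the unadjusted result as a sensitivity analysis and leave the exploratory age test as planned.

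The cost is a sentence or two of text and no new data. Two between-subject error degrees of freedom are lost. In an rmANOVA with 8 measurements, each covariate also takes 8 − 1 = 7 within-subject degrees of freedom, so the error falls from (64 − 2) × 7 = 434 to 420.

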### Power calculation

An a-priori power calculation was conducted using G*Power 3 [65] assuming a level of significance of *p *< 0.05, an effect size of f = 0.4 and two groups. The effect size of f = 0.4 was based on the study published by Bernhard et al. [32] and determined from the effect of TSST on CORT and OXT. The power analysis—when considering a correlation between CORT and OXT (as found by Bernhard et al. [32])—was conducted for a rmMANOVA (repeated measures Multivariate Analysis of Variance) and considered 8 measurements of CORT and OXT. Here, a sample size of 30 was estimated to achieve sufficient power of 80%. In case of no correlation between CORT and OXT, an rmANOVA (repeated measures Analysis of Variance) will be performed. Power analysis revealed that here a sample size of 8 will be required to achieve sufficient power of 80%. To determine the effects of group and sex on basal OXT and OXT increase through an additional MANOVA, a power analysis with an estimated effect size of f = 0.25 (medium sized effect) determined a total sample size of 64 (32 participants in each group). The latter sample size was chosen.

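### The MANOVA of baseline, increase and recovery names sex as a within-subject factor, which is impossible; the primary group comparisons also leave out age and pubertal status, on which the groups are matched

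*Protocol article*

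**What the plan says.** All references are to the protocol article.

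- Statistical analysis, on group differences in hormone baseline, increase and recovery: "MANOVAs will be computed with group as a between-subject factor and sex as a within-subject factor".
- The same section, on the demographic and psychometric data: an analysis "with group and gender as inter-subject factors".
- Power calculation: N = 64 (32 per group) was chosen for a MANOVA of group and sex effects on basal oxytocin and oxytocin increase, at f = 0.25.
- Eligibility criteria: "The healthy control group will be matched according to sex, age, pubertal status and school education".
- Physiological measures and stress challenge gives the purpose, "to minimize the effect of age and pubertal development", and the means: "both groups will be matched according to pubertal status".
- Age enters the hormone analyses only in exploratory FDR-corrected post-hoc work "testing for effects of sex and age on OXT and CORT reactivity will also be conducted". Pubertal status enters none of the analyses described. Sex is in the main MANOVA.
- The repeated-measures MANOVA for reactivity has time as its within-subject factor and group as its between-subject factor, with no covariates.

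**The concern.** A within-subject factor has levels at which the same person is measured more than once. Sex has no such levels. The sentence therefore describes a model that does not exist, and it is the one that answers the first primary question, whether basal oxytocin differs between groups. It is also the counterpart of the MANOVA used to set the sample size. A reader of the eventual report could not check that the analysis followed the plan, because literal adherence is impossible.

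The second part concerns efficiency. The protocol matches on age and pubertal status because it regards them as sources of hormone variation. If they do predict the hormone measures, a comparison that omits them leaves that variation in the error term, and the standard error of the group contrast is larger than it needs to be.

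**Working it through.** **1. Can sex be within-subject?** No participant contributes data at both levels, so no within-person sex contrast exists and the model has nothing to estimate.

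**2. Could it mean within matched pair?** No. Sex is one of the four matching variables, so it is constant within any matched pair.

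**3. Which reading do the other sections support?** Statistical analysis makes group and gender inter-subject factors for the descriptive data, and Power calculation refers to effects of group and sex. Both point to sex as a between-subject factor, in a 2 x 2 group-by-sex layout.

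**4. The plan's own figure.** With sex between-subject, f = 0.25, alpha 0.05 and 80% power (stated in the article for its other two calculations and assumed here), N = 64 does not reproduce. The two-outcome MANOVA needs 158 for the group effect (39.7% power at 64), and a single-outcome 2 x 2 ANOVA needs 128 (50.3% at 64). That is a separate matter. Correcting the factor label neither causes nor cures it, and nothing below depends on it.

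**5. Error degrees of freedom for the group contrast, per outcome.**
- Group and sex between-subject: 64 - 4 = 60.
- Adding age and pubertal stage as one linear term each: 60 - 2 = 58.
- Group tested within 32 pairs: 32 - 1 = 31.

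**6. Precision if controls are individually paired.** Let n be the number of pairs, s the standard deviation of the hormone measure and r the within-pair correlation. The article gives no value for r, so it is an assumption.
- Variance of the mean difference, unpaired: 2s²/n.
- Variance of the mean difference, paired: 2s²(1 - r)/n.
- Ratio of standard errors: sqrt(1 - r).

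| r (assumed) | sqrt(1 - r) | Reduction in standard error |
|---|---|---|
| 0 | 1.000 | 0% |
| 0.2 | 0.894 | 11% |
| 0.4 | 0.775 | 23% |

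The covariate route has about the same form, with the share of within-group variance explained by age and pubertal stage in place of r.

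**7. Direction of the error if pairs exist but are ignored.** This was simulated with 32 pairs, a two-sided 5% test and 100,000 runs per setting. The actual type I error of the unpaired test was 0.049, 0.038, 0.029, 0.020 and 0.007 at r = 0, 0.1, 0.2, 0.3 and 0.5. For a difference of d = 0.5 (f = d/2 = 0.25 with two equal groups), the unpaired test has about 50% power throughout. The paired test has 49%, 53%, 58%, 64% and 78%. Ignoring pairs is thus conservative, and at r = 0 pairing gains nothing.

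**The case against.** **It is a slip with one repair.** The inter-subject wording nearby makes the intention fairly clear, any analyst would have to enter sex between subjects, and the correction changes no hypothesis, outcome or data collection. This stands as far as consequences go. It does not make the sentence correct, and the sentence carries a primary comparison.

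**The matching may not be individual.** A reader might infer that the plan wrongly treats paired data as independent and so wastes the matching, or that group ought to be the within-unit factor. The documents do not support this. The article never states one-to-one pairing, and the sentence on pubertal status speaks of matching both groups. With frequency matching, group is properly between-subject and an independent-groups model is valid. Even with pairs, balance on the matched variables is kept and the loss is precision only.

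**The size is uncertain.** A reader might convert the table into equivalent unmatched samples: 64/(1 - 0.2) = 80 or 64/(1 - 0.4) = 107. Those figures need both individual pairs and a correlation the article does not give. The correlation could be near zero; the article itself notes that previous studies found no main effect of sex on adolescent oxytocin.

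**Covariates belong in the SAP.** A condensed article need not list every covariate, so the absence of age and pubertal stage is not an error. It is raised as an inexpensive improvement on the model the article states. The within-subject label is different, because the article states it outright.

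**Conclusion.** The specification of sex as a within-subject factor is wrong, contradicts the same section and must be corrected, since it belongs to the model for the first primary question. The repair is one phrase and there is little doubt about what was meant.

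The adjustment point holds in a limited form. The protocol matches on age and pubertal status for their effect on hormones but does not use them in any primary group comparison. Using them would buy precision; leaving them out does not invalidate the comparison. The gain depends on the unstated type of matching and on how strongly age and puberty predict the hormone measures. It ranges from nothing to a standard error about 23% smaller over the assumed correlations of 0 to 0.4.

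**What to change.** 1. In Statistical analysis, change the factor description for the baseline, increase and recovery MANOVAs to 'group and sex as between-subject factors'. This costs nothing.
2. State whether controls are matched one-to-one or by group distribution.
3. Add age and stage on the Pubertal Development Scale as covariates in the primary group comparisons. Both are already collected. The cost is about two error degrees of freedom if each enters as a single linear term.
4. If controls are individually paired, the alternative is to test group within pairs. This leaves about 31 error degrees of freedom instead of about 60, and needs a model with a pair term or an analysis of within-pair differences, so it is more than a wording change. Choose one route before the data are analysed.
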